Measurements Activity 2: At T0, we will collect sociodemographic and data clinical from patients, including age, gender, sex, occupation, marital status, socioeconomic status and clinical diagnosis. We will also assess participants' expectations in the form of the question do you have any expectations regarding the use and efficacy of RVH? . At T0, T2 and T3, we will collect data on quality of life, anxiety, pain, fatigue and depression. The FACT-BMT is a validated scale for patients undergoing bone marrow transplantation. It contains 50 items divided into 5 subscales: Physical Well-Being, Social/Family Well-Being, Emotional Well-Being, Functional Well-Being and Bone Marrow Transplant Subscale on a 5-point Likert scale ranging from 0 = not at all to 4 = very much. The *Hospital Anxiety Depression Scale* (HADS) is a scale validated in French for cancer, which assesses participants' anxiety-depression. It is made up of 14 items: 7 items determine the degree of anxiety and the other 7, the degree of depression. The score of each subscale is calculated by summing the score of each item, which varies between 0 and 3, with each subscale reaching a maximum score of 21. Fatigue will be assessed using the 10-item version of the Multidimensional Fatigue Inventory (MFI-10) adapted to cancer. It is scored on a 5-point Likert scale ranging from 1: "strongly disagree" to 5: "strongly agree". Pain is assessed using the Brief Pain Inventory (BPI). This scale consists of 8 items on a 10-point Likert scale assessing pain severity, impact of pain on daily functions, location of pain, pain medication and extent of pain relief over the past 24 hours or week. At transplantation, we will use the diary with 11-level Scales before and after each RVH procedure to assess the direct effect of the procedure on pain, anxiety, enjoyment, i.e., the ability to enjoy oneself during the intervention, absorption, i.e., the tendency to become totally involved in a perceptual and imaginative experience, dissociation, i.e., a mental separation of components of the experience and fatigue. After each intervention, the Simulator Sickness Questionnaire, a scale validated in French, assesses symptoms of cybermalaise linked to immersion in VR. It contains 16 items divided into two subscales: nausea and oculomotor, which the participant must qualify as "not at all" (score 0), "a little" (score 1), "moderately" (score 2) or "severely" (score 3). . At T3, we will collect patients' level of satisfaction through a 19-item questionnaire that is evaluated on an 11-point Likert scale (0 = "strongly disagree" and 10 = "strongly agree" with the proposal). This questionnaire has been used in other studies to assess participant satisfaction with an intervention program^37. We will collect patients' levels of expectation and satisfaction using a five-level rating scale (1 = "not at all satisfied", 5 = "very satisfied") and explanatory interviews. Satisfaction interviews will also be conducted with caregivers in the hematology departments involved. The outcome secondary will be the change from T0 to T2 and T3 in the scores FACT-BMT, MFI and HADS-D, while the main outcomes primary will be changes from T0 in the degree of anxiety, of pain, . Changes in measures of pain, anxiety, amusement, absorption, and dissociation (logbooks completed during the two-week transplant stay) will also be considered secondary outcomes. We expect to At T3, we will assess acceptability and user experience with the User Questionnaire Experience (UEQ). This validated questionnaire is composed of 24 items that are evaluated on a 7-level Likert scale. It will be used to assess the six components of user experience: usability, usefulness, hedonic qualities (e.g., originality), attractiveness, sense of presence, resulting emotions. Sample size justification: At HMR, around 100 patients a year are treated for multiple myeloma and undergo cell transplantation stem. The sample size was also determined using a power calculation to ensure a sufficient probability of detecting a statistically significant effect, if any. We used an alpha significance level of 0.05 and a power (1 - B) of 0.95. The expected effect was estimated from \_\_\_\_\_, with an effect size of \_\_\_\_\_. Based on these

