#### *Quantitative*

In order to evaluate the efficacy of the intervention in the experimental group compared to the control group, a MANCOVA will be performed. The dependent variables are anxiety, depression, pain, quality of life and fatigue, and the independent variables are the different measurement times. We will control for the following : gender, age, socioeconomic status, diagnosis, absorption, dissociation and enjoyment. We will make post-hoc comparisons to compare scores between groups and at each measurement time. They will be made with a correction covariates Bonferroni .

Correlations will be performed on variables measured during the transplant phase, to measure the immediate effects of RVH.

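### The efficacy MANCOVA does not adjust for the T0 score of each outcome, although T0 is collected, so precision is lost whether changes or follow-up scores are analysed

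*Protocol*

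**What the plan says.** Protocol, section 3, Measurements Activity 2, sets the schedule: "At T0, T2 and T3, we will collect data on quality of life, anxiety, pain, fatigue and depression". It defines the outcomes as changes. For the primary outcomes, "the main outcomes primary will be changes from T0 in the degree of anxiety", with pain named next. For the others, "The outcome secondary will be the change from T0 to T2 and T3 in the scores FACT-BMT, MFI and HADS-D".

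Section 3, Analysis activity 2, Quantitative, names the method: "In order to evaluate the efficacy of the intervention in the experimental group compared to the control group, a MANCOVA will be performed". It then says: "The dependent variables are anxiety, depression, pain, quality of life and fatigue, and the independent variables are the different measurement times". The adjustment is a stated list: "We will control for the following : gender, age, socioeconomic status, diagnosis, absorption, dissociation and enjoyment". Post-hoc comparisons between groups and at each measurement time follow, with a Bonferroni correction, and these are described as comparisons of scores.

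So one section defines changes and the other speaks of scores. Neither puts the T0 value of an outcome among the covariates.

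**The concern.** The T0 value of a questionnaire score often predicts the later value of the same score well. Here it is already planned for every participant and every outcome. The plan uses it at most to form a difference or as one of the measurement times.

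The listed covariates do not replace it. Four are demographic or diagnostic. Absorption, dissociation and enjoyment are recorded in the transplant-stay diary, for which "we will use the diary with 11-level Scales before and after each RVH procedure". They are therefore measured after randomisation, and no control-arm measurement of them is described.

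At stake is the width of the confidence interval for the arm difference in a trial of 60 patients. Because the Protocol itself fixes the method and the covariates, this is more than a detail left to a statistical analysis plan.

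**Working it through.** **The plan's own figure.** The total of 60 (alpha 0.05, power 0.95) cannot be reproduced, because no effect size or loss rate is given in the text. It therefore does not show which form of analysis the sample size assumed.

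**Inputs.**
- From the Protocol: 60 patients allocated 1:1, so n = 30 per arm; "We used an alpha significance level of 0.05", with sidedness not stated and taken here as two-sided.
- Assumed: correlation r between T0 and follow-up of 0.3, 0.5 or 0.7; equal SDs at T0 and follow-up; an arm difference of 0.5 SD for the power illustration.
- Other covariates are ignored. With them in the model, r becomes the correlation left after adjusting for them.

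**Three readings of the analysis section.** Arm is taken to be a factor on each, since the stated purpose is a between-arm comparison.
1. Changes from T0 are the dependent variables.
2. Scores at T0, T2 and T3 are analysed with T0 as a level of time. The arm-by-time contrast of T2 (or T3) with T0 is then still a difference in mean change.
3. Only T2 and T3 scores are compared. T0 is not used.

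**Formulas.** The variance of the arm difference is v × (2/n) × SD², with
- follow-up score alone: v = 1;
- change: v = 2(1 − r);
- T0 score as covariate: v = 1 − r².

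The ratio of adjusted to change is (1 − r²) / [2(1 − r)] = (1 + r)/2. The ratio of adjusted to follow-up alone is 1 − r².

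| r | v, follow-up | v, change | v, T0-adjusted | Cut against change | Cut against follow-up |
|---|---|---|---|---|---|
| 0.3 | 1 | 1.40 | 0.91 | 35% | 9% |
| 0.5 | 1 | 1.00 | 0.75 | 25% | 25% |
| 0.7 | 1 | 0.60 | 0.51 | 15% | 49% |

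**In patients.** Sixty patients analysed as changes give the precision of 60 × (1 + r)/2 = 39, 45 or 51 analysed with the T0 covariate. Sixty analysed on follow-up scores alone give that of 60 × (1 − r²) = 54.6, 45 or 30.6.

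**In power** (difference 0.5 SD, 30 per arm, two-sided 0.05, normal approximation, before any Bonferroni correction):

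| r | Follow-up alone | Change | T0-adjusted |
|---|---|---|---|
| 0.3 | 49% | 37% | 53% |
| 0.5 | 49% | 49% | 61% |
| 0.7 | 49% | 71% | 77% |

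Change beats the follow-up score only when r is above 0.5. The T0-adjusted analysis is at least as precise as either at every r shown, so it removes the need to guess.

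**The case against.** The strongest reply is that this is only an efficiency matter. Randomisation makes both the change comparison and the follow-up comparison unbiased on average, and the gain depends on a correlation that the document does not give. On the change reading it falls to 10% at r = 0.8. That stands, and it limits the point to precision.

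A reader might infer more in three ways, and the document does not support any of them.

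- *That change scores are definitely what enters the MANCOVA.* The outcome definitions say change, but the analysis section names the outcomes themselves and its post-hoc step compares scores. The (1 + r)/2 gain is therefore one reading, and both must be shown.
- *That partly observed patients are discarded.* Standard MANCOVA drops incomplete cases by default, but the Protocol does not say so. Comparisons at each measurement time could use a patient with T2 only, and an unseen statistical analysis plan could add another method. Any count is also pattern-dependent. With 5–15% missing independently at each of T2 and T3, 60 × (1 − m)² gives 54 to 43 complete cases. If the only loss is drop-out reaching 5–15% by T3, it is 57 to 51. This is a secondary reason for the model below, not a stated defect.
- *That a serious T0 imbalance is likely and would distort the result.* With 30 per arm the standard error of a T0 difference is √(2/30) = 0.26 SD, so a gap above 0.5 SD has about a 5% chance per outcome.

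It is also fair to object that the remedy is not free. It replaces one multivariate test with a model per outcome and needs its own assumptions.

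**Conclusion.** The point holds as a loss of precision. A stated covariate list leaves out the T0 outcome scores although they are collected, and adding them reduces variance on every reading of the analysis section. For r between 0.3 and 0.7 the reduction is 35% down to 15% if changes are compared, or 9% up to 49% if follow-up scores are compared. These sizes rest on assumed correlations, equal SDs and no other covariates; the power figures rest in addition on an illustrative difference of 0.5 SD.

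The mismatch between change and score across the two sections is a separate fact that needs no assumption, and it has to be settled before the estimate can be defined. The document supports neither a claim of bias nor a claim that patients are excluded.

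**What to change.** 1. Reconcile Measurements Activity 2 with Analysis activity 2 so that both state the same quantity: the arm difference in the T2 and T3 score of each outcome, adjusted for the T0 score of that outcome. Change from T0 can still be reported descriptively.
2. Preferably fit, for each outcome, a likelihood-based repeated-measures model to the T2 and T3 scores. Include arm, time, arm × time, the matching T0 score, T0 × time and the baseline covariates (gender, age, socioeconomic status, diagnosis). Include every randomised patient with at least one follow-up score, in the allocated arm.
3. Keep the Bonferroni correction and say which comparisons it covers, since separate models replace the single multivariate test.
4. Say openly that absorption, dissociation and enjoyment are not in this model because they are not baseline variables.

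The cost is protocol wording, one degree of freedom per outcome at each follow-up visit, and the loss of the overall multivariate test. The model assumes that missing scores are missing at random given the observed data, which should be stated, and patients with no follow-up score still contribute nothing. No extra data are needed.

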Procedures activity 2: As shown in figure 2, participants will be randomly assigned in a controlled manner with a ratio of 1:1 to two conditions: RVH and a control condition (C) consisting of usual care and a waiting list. This allocation will be done by a random draw using the *Research Randomizer* program (<https://www.randomizer.org/>), which will be conducted by a person independent of the study. The first meeting will take place on arrival at the hospital, where the study presentation will take place, and the consent form will be signed. Participants will be asked to complete self-assessments at three time points: T0=pre-, session T1=accompanied, and T2=post-transplantation (1 months) and at T3=follow-up (3 months). According to studies carried out on multiple myeloma patients, T1 is conducted between D-14 and D-1 of the transplant stay.

[figure not shown]

Measurements Activity 1: We will use two questionnaires. The first assesses the participant's satisfaction through a questionnaire 19-item, which is evaluated on an Likert scale 11-level (0 = "strongly disagree" and 10 = "strongly agree" with the proposition). A questionnaire (UEQ, 24 items, 7-level Likert) will also be used to assess the six components of user experience: usability, usefulness, hedonic qualities (e.g., originality), attractiveness, sense of presence, resulting emotions. The interview grid will be based on the same items as these questionnaires, enabling participants to develop their responses.

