
parameters, the power calculation suggests that a sample size of 60 participants is required to detect this effect with adequate power. The software \_\_\_\_ was used to perform this calculation. The sample size also takes into account a potential loss rate of \_\_\_\_%, to compensate for drop-outs and missing participants. .

Analyses Activity 1: The scores obtained on the questionnaire items will be compared with the theoretical mean of 6, i.e. the neutral level of acceptability on a scale from 0 to 10. An average above this threshold will be interpreted as a good experience of RVH. Analysis of the interview verbatim will enable us to make an open-ended assessment of the RVH experience. Significant narratives in each theme will be used to illustrate participants' opinions and experiences. Qualitative analysis of the narratives will enable us to identify positive and negative aspects, as well as avenues for improving the program. NVIVO software will be used for these analyses. This study will enable relevant modifications to be made to the program prior to the clinical effects study.

Analysis activity 2 :

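### The 95% power claimed for 60 patients is set at an uncorrected alpha of 0.05, while two primary outcomes and Bonferroni-corrected comparisons imply about 86% to 91% for the same effect

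*Protocol*

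**What the plan says.** All places are in Protocol section 3, Methodologies.

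- **Error rates.** The sample size justification states: "We used an alpha significance level of 0.05 and a power (1 - B) of 0.95". It gives no sidedness and does not divide alpha between outcomes.
- **Sample size.** It concludes that "the power calculation suggests that a sample size of 60 participants is required to detect this effect with adequate power". It then adds: "The sample size also takes into account a potential loss rate of", followed by a blank. The effect size, its source and the software are also blank, and no test is named.
- **Allocation.** Under the Activity 2 procedures, "participants will be randomly assigned in a controlled manner with a ratio of 1:1 to two conditions", so 30 per arm.
- **Outcomes.** The Activity 2 measurements name two primary outcomes, the changes from T0 in anxiety and in pain. No single primary time point is chosen; the questionnaires are repeated at T2 and T3.
- **Analysis.** The Quantitative subsection plans a MANCOVA on five outcomes (anxiety, depression, pain, quality of life, fatigue). Post-hoc comparisons between groups and at each time follow, and of these it says: "They will be made with a correction covariates Bonferroni". The number of comparisons in the correction is not given.

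**The concern.** A power figure holds for one test at one significance level. Here it is given for a single test at 0.05, whereas the plan's only stated between-group comparison of anxiety or pain taken singly is a corrected post-hoc test. The same 60 patients tested at a smaller alpha have less power for the same effect, and the sample-size text makes no allowance for this.

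The stake is how the result is read. A reader told that the trial had 95% power will give a non-significant result on anxiety or pain more weight than it deserves, all the more because 30 per arm reaches 95% only for a large effect, and the text shows no effect size to warn of this.

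**Working it through.** **Inputs from the protocol:** alpha 0.05, power 0.95, total 60, ratio 1:1, two primary outcomes, later assessments at T2 and T3, Bonferroni correction of post-hoc comparisons.

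**Assumptions:** two-sided two-sample t-test; losses of 10% to 20% where a loss is needed; baseline correlation r of 0.5 or 0.7 where adjustment is considered.

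**Formula.** With n per arm and standardised effect d, the noncentrality is δ = d·√(n/2) on 2n − 2 degrees of freedom. Power is the probability that a noncentral t with that δ falls beyond ±t(1 − α/2).

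**Step 1: the plan's own figure.** The 60 cannot be reproduced forwards, because the effect size is blank. Solving backwards with n = 30, α = 0.05 and power 0.95 gives d = 0.947. Check: δ = 0.9466 × √15 = 3.67 against a critical value of 2.00 on 58 df, power 0.950.

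If the 60 already includes losses, the evaluable number is smaller and the implied effect larger:
- 10% loss, 27 per arm: d = 1.00
- 20% loss, 24 per arm: d = 1.06

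**Step 2: the same effect at a corrected alpha.** Two primaries give 0.05/2 = 0.025. Two primaries at T2 and T3 give 0.05/4 = 0.0125. Each row uses the effect that has 95% power at 0.05 for that n.

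| Evaluable per arm | Effect (SD) | Power at 0.05 | at 0.025 | at 0.0125 |
|---|---|---|---|---|
| 30 | 0.947 | 0.950 | 0.911 | 0.858 |
| 27 | 1.00 | 0.950 | 0.910 | 0.857 |
| 24 | 1.06 | 0.950 | 0.910 | 0.855 |

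For n = 30, δ stays at 3.67 while the critical value rises from 2.00 to 2.30 and then 2.58. The rows barely differ, so under this test the shortfall depends neither on the blank effect size nor on whether losses sit inside the 60.

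**Step 3: baseline adjustment.** ANCOVA on T0 multiplies the detectable effect by √(1 − r²). With all 60 evaluable at 0.05:
- r = 0.5: 0.947 × 0.866 = 0.82 SD
- r = 0.7: 0.947 × 0.714 = 0.68 SD

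**Step 4: power at 0.5 SD, 30 per arm.**

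| Analysis | α = 0.05 | α = 0.025 |
|---|---|---|
| Unadjusted | 48% | 36% |
| Adjusted, r = 0.5 | 59% | 48% |
| Adjusted, r = 0.7 | 76% | 66% |

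All these figures are far from 95%.

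**The case against.** The best defence is that the power statement may refer to the MANCOVA. The Bonferroni correction is attached to the post-hoc comparisons, and power stated for a main test need not carry a post-hoc correction. With the effect size and test unstated, delivered power cannot be computed at all. This stands in part: the 91% and 86% are conditional on a t-test and on a chosen split of alpha. It does not rescue the claim, because the MANCOVA pools five outcomes, three of them secondary, and lists measurement times rather than group as its independent variables. It does not test anxiety or pain singly between groups; the corrected comparisons do.

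Four stronger readings are tempting, and the protocol does not support them.

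- **The statements about losses contradict each other.** A reader might infer this because 60 is both the required number and a number that allows for losses. The ordinary reading is that 60 is the recruitment total after that allowance, and the Activity 2 text does plan to recruit 60. The wording is loose, not contradictory.
- **Losses should be taken off the 60 again.** Subtracting a loss from a total said to include it counts the loss twice. If 60 is the inflated total, the consequence is a larger implied effect (step 1), not a further fall in power.
- **The correction covers 15 comparisons (five outcomes at three times).** No such family is written. It would include T0, where no treatment effect is sought, and three secondary outcomes.
- **A moderate effect would be missed more often than found.** At 0.05 and 0.5 SD this holds without baseline adjustment (48%) but not with it (59% to 76%). It cannot be stated generally.

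**Conclusion.** The point holds in a limited form. The stated 95% belongs to an uncorrected alpha of 0.05 and is not tied to the two primary outcomes or to the corrected comparisons that would test them. Under a two-sided two-group t-test the same effect has about 91% power at 0.025 and about 86% at 0.0125, whichever evaluable number was used. The shortfall is therefore 4 to 9 percentage points.

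The implied effect is large under the simple test, at 0.95 SD with all 60 evaluable or 1.00 to 1.06 SD with an assumed 10% to 20% loss inside the 60. With baseline adjustment and all 60 evaluable it is about 0.82 or 0.68 SD (r = 0.5 or 0.7).

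The test, its sidedness, the split of alpha, the loss rate and the correlation are assumptions. The exact delivered power stays unknown until the protocol fixes them. The mismatch between the alpha used for power and the corrected comparisons does not depend on the blank fields.

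**What to change.** Keep 60 patients and rewrite the sample-size paragraph so that it:

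1. says whether 60 is the recruited or the evaluable number, and gives the loss rate;
2. sets the alpha, sidedness and time point or points for each primary comparison;
3. names the test, and the effect size with its source;
4. replaces the 95% statement with the power, or the detectable effect, at that alpha and evaluable number.

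Example, assuming 20% loss and two-sided 0.025 per primary outcome: 60 randomised, 60 × 0.8 = 48 evaluable (24 per arm), 80% power for 0.92 SD and 95% power for 1.15 SD, before T0 adjustment. If a gain from T0 adjustment is claimed, state the correlation assumed.

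The cost is wording and a less favourable stated figure; no patients are added. Holding 95% power for the 0.947 SD effect would instead need 72 evaluable patients at 0.025, or 72/0.8 = 90 enrolled at 20% loss. Restating the figure is the lighter course.

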#### *Evaluation of the RVH program user experience*

**Participants:** A mixed study, combining quantitative and qualitative designs, was conducted with 40 partner patients in remission from cancer and 5 hospitalized hematology patients. For Activity 2, 60 participants will be recruited at the Maison-Neuve-Rosemont Hospital oncology, after verification of eligibility in the medical records and with the attending physician, who will have received prior authorization from the patient to be contacted by the research team. Inclusion criteria for participants are: 18 years of age or older, French-speaking, being treated for lymphoma or myeloma and requiring a hematology transplant. Exclusion criteria are: deafness, blindness, confusion or other disorders that may impair communication.

**Procedures Activity 1:** As shown in figure 1, two sequences will be conducted. In the first sequence, partner patients in remission from cancer will be invited to experiment with and give feedback on the program in order to improve the RVH device, based on their personal experience. In the second phase, a pre-test of RVH will be carried out with patients hospitalized for a hematology transplant. These two sequences will consist of three stages. Participants will be invited to 1- use the RVH intervention in the company of a psychologist; 2- complete a questionnaire evaluating the user's experience; 3- take part in individual semi-structured interviews, conducted by a duo made up of a patient partner and a researcher, in order to gather explanations complementary to the scores attributed in the questionnaires.

**Figure 1:** Activity 1 protocol: User experience study

[figure not shown]

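### The Activity 1 rule calls 6 the neutral level of a 0-10 scale whose midpoint is 5, so it is stricter than its own definition

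*Protocol*

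**What the plan says.** Under Measurements Activity 1 (Protocol, section 3), two questionnaires are named. The first is a 19-item satisfaction questionnaire with 11 levels, anchored at "0 = 'strongly disagree' and 10 = 'strongly agree' with the proposition". For the second, the text says: "A questionnaire (UEQ, 24 items, 7-level Likert) will also be used".

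Under Analyses Activity 1, the item scores "will be compared with the theoretical mean of 6, i.e. the neutral level of acceptability on a scale from 0 to 10". The decision rule follows: "An average above this threshold will be interpreted as a good experience of RVH". No other numerical criterion is given for Activity 1, and no reason is offered for a cut-off above the middle of the scale.

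The sample is described under Participants in the past tense: the study "was conducted with 40 partner patients in remission from cancer and 5 hospitalized hematology patients".

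**The concern.** The sentence gives one number two descriptions, theoretical mean and neutral level, and ties both to a scale from 0 to 10. On that scale neither description fits 6. The number and its definition conflict, and the number is the one used to label the result.

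At stake is how the satisfaction scores are read. An item or questionnaire mean that is on the favourable side of true neutral, but not above 6, would fail a test presented as a comparison with neutrality. A reader of the report would take this to mean that patients were neutral or unfavourable when the scores say otherwise.

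**Working it through.** **Inputs.**
- Stated neutral level: 6 (Analyses Activity 1).
- Scale of the satisfaction items: 0 to 10, 11 levels (Measurements Activity 1). The same range is repeated in the sentence that contains the threshold.
- Activity 1 sample: 40 patients in remission and 5 hospitalised patients (Participants).
- Standard deviation of the scores: not given. A range of 1.5 to 2.5 is assumed below, for illustration only.

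**Step 1: try to reproduce 6.** The midpoint of equally spaced levels is (minimum + maximum)/2, which is also the mean of the levels.

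| Coding | Midpoint |
|---|---|
| 0 to 10 (as stated) | (0 + 10)/2 = 5 |
| 1 to 10 | (1 + 10)/2 = 5.5 |
| 1 to 11 | (1 + 11)/2 = 6 |

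Only a 1-11 coding gives 6. On the stated coding the middle level is the sixth of the 11, and its value is 5. Confusing the rank of the middle level with its value would explain the figure, but the protocol does not say how 6 arose.

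**Step 2: size of the displacement.** 6 - 5 = 1 point. The favourable half of the scale runs from 5 to 10, so the rule excludes (6 - 5)/(10 - 5) = 20% of that half. Because an average must be above the threshold, a mean of exactly 6 is excluded too.

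**Step 3: effect on the label, as an illustration.** Take a true mean of 5.5, half a point on the favourable side, with n = 40. Under a normal approximation, the standard error is SE = SD/√40, and
- P(sample mean > 5) = Φ(0.5/SE)
- P(sample mean > 6) = 1 - Φ(0.5/SE)

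| Assumed SD | SE | 0.5/SE | P(mean > 5) | P(mean > 6) |
|---|---|---|---|---|
| 1.5 | 0.237 | 2.11 | 0.98 | 0.02 |
| 2.0 | 0.316 | 1.58 | 0.94 | 0.06 |
| 2.5 | 0.395 | 1.26 | 0.90 | 0.10 |

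For scores in this band the choice between 5 and 6 usually reverses the label. If the true mean is well above 6, the choice makes no practical difference: at 6.5, the probability of exceeding 6 is already 0.90 to 0.98 over the same SD range.

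**The case against.** **A stricter cut-off is legitimate.** An investigator may ask for more than neutrality before calling an experience good, and 6 would be a reasonable bar. That is true, but the protocol does not say so. It defines 6 as the neutral level and the theoretical mean, and gives no rationale for a higher target. This defence shows one way to repair the text and does not remove the conflict.

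**The reach is small.** Most of this objection stands.
- The error makes a favourable label harder to obtain and cannot inflate one.
- The rule belongs to Activity 1, which section 2 (Objectives) and the Participants paragraph describe partly as completed, although other sentences use the future tense.
- The randomised comparison of Activity 2, its outcomes and its sample size of 60 do not depend on the rule.

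**Stronger readings that a reader might infer, and that the protocol does not support.**
- *That UEQ items would be judged against 6.* The sentence mentions the questionnaire items without naming one, but it limits itself to a 0-10 scale, and of the two Activity 1 questionnaires only the satisfaction one has that scale. A UEQ reference value is absent rather than wrong, and may properly be left to a statistical analysis plan.
- *That the threshold decides which parts of the program are changed.* The protocol says "This study will enable relevant modifications to be made to the program prior to the clinical effects study", but it assigns the search for improvements to the qualitative analysis of the interviews. No modification or stop/go decision is tied to 6.
- *That the same cut-off applies at T3.* The instruments recur there, but no text carries the rule over to Activity 2.
- *That the rule ignores sampling error.* A comparison with a reference mean is compatible with a one-sample test. The choice of test or confidence limit can be left to a statistical analysis plan.

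**Conclusion.** The point holds for the 0-10 satisfaction questionnaire. As written, 6 cannot be the neutral level or theoretical mean of a scale from 0 to 10; that value is 5. The threshold is 1 point too high for its stated meaning, and means above 5 and up to 6 would be denied a favourable reading that the scale itself supports.

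This takes neutral to mean the arithmetic midpoint. The protocol's term theoretical mean implies as much, although only the two ends of the scale carry verbal anchors. The midpoint result needs no assumption about variability. The probabilities in the illustration do depend on the assumed SD of 1.5 to 2.5 and on n = 40.

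This is a definite but limited error: conservative in direction and confined to the Activity 1 user-experience interpretation. It gives no ground for doubting the randomised part of the trial.

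**What to change.** In Analyses Activity 1, do one of the following:
- replace 6 by 5 as the neutral reference for the 0-10 satisfaction items; or
- keep 6, call it a stricter target above the neutral level of 5, and give the reason for choosing it.

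In the same sentence, state that the rule applies to the 19-item satisfaction questionnaire scored 0 to 10 and not to the 7-level UEQ.

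If Activity 1 has already been analysed against 6, report the means against 5 as well and say when the threshold was corrected. The cost is a wording change and, at most, a re-reading of means already computed. No new data are needed, and neither the design nor the sample size changes.
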